# Definitions

| Term | Definition |
| --- | --- |
| Baseline values | Directly after the written informed consent a blood sample will be taken for the baseline measurements (laboratory baseline values). |
| Age | The age is calculated using the date of informed consent and date of birth. If the day of the birth date is unknown, it is set to 15. If day and month are missing the 1st of July is considered as the date of birth. |
| D0, D1, D2, D3, D7, D14 and D28 | For the definition of days the latest WHO Definition is used (WHO 2003).  D0= calendar day of the first treatment, D1= first calendar day after the calendar day of first treatment. This definition is used for the endpoints ETF, LCF, LPF, ACPR and fever or parasite clearance time. D7, D14, D28 is defined as the 7th, 14th and 28th day after first drug intake, with a tolerance of –1 and +3 days. |
| ETF | - Danger signs or severe malaria on D1, D2 or D3 + parasitemia - Parasitemia on D2 > D0 count irrespective of axillary temperature - Parasitemia on D3 ≥ 25% of count on D0 |
| LCF | - Development of danger signs or severe malaria after D3 in the presence of parasitemia, without meeting any of the criteria of ETF - Presence of parasitemia + axillary temperature ≥37.5°C on any day from D4 to D28, without previously meeting any criteria of ETF |
| LPF | - Presence of parasitemia on any day from D7 to D28 + axillary temperature <37.5°C, without previously meeting any of the criteria of ETF |
| ACPR | - No parasites on D28 irrespective of axillary temperature without previously meeting any of the criteria of ETF, LCF or LPF |
| Fever clearance | Time between fever at inclusion and first temperature < 37.5°C |
| Parasite clearance | Time between inclusion and time where no more parasites are detectable |
| Recrudescence | Re-emerging of the same *P. falciparum* strain from D14 to D28 according to PCR genotyping |
| Reinfection | New infection from D14 to D28 according to PCR genotyping |
| AEs | The adverse event (=AE) defined in chapter 12 is used, but blue urine is expected for all children in the MB-AS and MB-AQ treatment groups. Only AEs after initiation of study treatment will be tabulated. |
| SAE | The definition of serious adverse event (SAE) is given in chapter 11 |
| Haemolysis | Any drop in haemoglobin (Hb) of >2.5 g/dl within 24 hours |
| Severe acute haemolysis | Hb  5 g/dl or received blood transfusion according to clinical judgement of study physician. |

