# Definition of outcomes

Primary endpoint:

- Incidence of observed and self-reported non-serious adverse events over the 28 days observation period (definition chapter 11)

Secondary endpoints:

- Incidence of serious adverse events (definition: chapter 11) over the 28 days observation period
- ACPR rate until D28
- Early treatment failure (ETF) rate
- Late clinical failure (LCF) rate at D14 and D28
- Late parasitological failure (LPF) rate at D14 and D28
- Fever clearance time
- Parasite clearance time
- Change in haematocrit after 2, 3, 7, 14 and 28 days compared to baseline

*Justification:* SAE rates and clinical and parasitological failure rates as well as fever and parasite clearance times are standard endpoints to judge the safety and efficacy of antimalarial drugs. This information will be relevant to plan future phase III trials.

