# Selection and withdrawal of subjects

Sample size

180 children (60 children in each of the three different treatment regimens) will be enrolled into the study. The sample size of 60 per arm enables us to demonstrate a difference in AE rates of 10 % with 90% power and at a 0.05 significance level.

Inclusion criteria

- 3-4 year (36-59 months) old children
- Between 10 kg and 22.5 kg body weight
- Ability to swallow tablets
- Uncomplicated malaria caused by *P. falciparum*
- Asexual parasites ≥ 2000/µl and ≤ 200000/µl
- Axillary temperature ≥ 37.5°C
- Burkinabe nationality
- Informed consent

Exclusion criteria

- Complicated or severe malaria
- Any apparent significant disease
- Anaemia (haematocrit < 21%)
- Treated in the same trial before
- Antimalarial treatment prior to inclusion (last three days), except children having been treated with chloroquine

Withdrawal criteria

Participants may be withdrawn from the study at their guardians request and any change in the patient’s condition which in the investigator’s opinion, for reasons of safety or ethics, precludes further participation in the trial. In case of vomiting after the repeated drug intake (one repetition only) of the first drug ingestion, the participant will be withdrawn from the study. Subjects withdrawn from the study during the first 3 days will be replaced.

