# Treatment of subjects and clinical study procedures

Description of the treatments

All patients in the MB-AS group will receive for 3 days twice daily (morning and evening) 10mg/kg MB accompanied by once daily (morning) 4mg/kg artesunate (= 4mg/kg total daily dose).

MB will be given according to the following weight table:

10,0 – 16,0 kg = 130mg = 2 tablets per treatment = 2 x 2 tablets /day

16,5 – 22,5 kg = 195mg = 3 tablets per treatment = 2 x 3 tablets/ day

AS will be given according to the following weight table:

10,0 – 16,0 kg = 50mg = 1 tablet per treatment = 1 tablet per day

16,5 – 22.5 kg = 100mg = 2 tablets per treatment = 2 tablets per day

AQ will be given according to the following weight table:

10,0 – 16,0 kg = 100mg = 1 tablet per treatment = 1 tablet per day

16,5 – 22.5 kg = 200mg = 2 tablets per treatment = 2 tablets per day

Product description

MB (Urolene Blue®, Star Pharmaceuticals, USA); 1 tablet Urolene Blue® = 65mg)

AS (Artesunate®, Guilin Pharmaceuticals Co., Ltd., China; 1 tablet Artesunate® = 50mg)

AQ (taken from the essential drug store of the Ministry of Health, Burkina Faso; 1 tablet amodiaquine=100mg)

Concomitant treatments

Patients having received antimalarial treatment prior to inclusion (last three days) will be excluded except children having been treated with chloroquine.

All children having fever ≥ 38.5°C will receive standard doses of paracetamol (= acetaminophen; 10 mg/kg) until symptoms subside (taken from the essential drug stock of the Ministry of Health, product description: paracetamol tablets or syrup).

All indicated drugs are allowed, except other western antimalaria drugs, antibiotics with antimalarial efficacy, acetanilide and phenacetin, nalidixic acid, niridazole, nitrofurantoins and sulphonamides (or any other drug that might induce haemolysis in G6PD deficient individuals) from beginning of treatment until end of follow-up.

Prior and concomitant illnesses

History of prior illnesses will become investigated and recorded. All relevant concomitant illnesses will be recorded based on the examination of the study physicians at D0, D1, D2, D3, D7, D14 and D28.

Procedures for monitoring subject compliance

Drug intake will be directly monitored by a study nurse or a field worker for the whole treatment period, supervised by the study physicians.

Visits and treatment schedule

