After identification of febrile children in the specified age group in the community, enrolled children are treated and supervised as outpatients according to the study flow explained in chapter 3. Children are examined at regular intervals (D0, D1, D2, D3, D7, D14 and D28) by a study physician. In case of not coming to the clinic on respective examination days, children will be visited at home by field staff. Parents/guardians are instructed to return to the hospital in case of worsening of their child’s clinical condition at any time during the follow-up period.

Day 0

- Presentation of the febrile child at one of the fever measurement points
- Informed consent
- Baseline status (weight, temperature)
- Examination 1 (at the Nouna district hospital)
- Questioning for inclusion/exclusion criteria
- Capillary blood sample for a thin and thick blood film (malaria) and haematocrit
- 1 filter paper is kept for genotypic determination of G6PD deficiency
- 1 filter paper is kept to distinguish between recrudescence and reinfection according to PCR during follow-up
- Treatment 1 (before 14:00) – MB-AS or MB-AQ or AS-MB
- Treatment 2 (evening) – MB

Day 1

- Examination 2 (morning)
- Treatment 3 (morning) – MB-AS or MB-AQ or AS-MB
- Treatment 4 (evening) – MB

Day 2

- Examination 3 (morning)
- Capillary blood sample (parasitemia and haematocrit)
- Treatment 5 (morning) – MB-AS or MB-AQ or AS-MB
- Treatment 6 (evening) – MB

Day 3

- Examination 4 (morning)
- Capillary blood sample (parasitemia and haematocrit) (morning)

Day 7, 14 and 28

- Examination 5, 6 and 7 respectively (morning)
- Capillary blood sample for parasitemia and haematocrit

Other time periods

- Phaenotypical G6PD determination and further investigations according to study physicians judgement will take place at any day between D0 and D28 in case of haemolysis
- 1 filter paper is kept to distinguish between recrudescence and reinfection according to PCR during follow-up (D7, 14, 28 and any other day the child returns for examination between D3 and D28)

Clinical management of (serious) adverse events

Study physicians and emergency medications will be available 24h to deal with SAEs. Additional laboratory tests are available 24h if needed and a standard blood transfusion service is established at the hospital (e.g. in case of haemolysis).

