# Assessment of secondary endpoints

Specification of parameters

- Number and proportion of patients with at least one serious adverse event:
  1. acute haemolysis (definition: haemoglobin  5 g/dl and haematocrit  15%, or received blood transfusion according to clinical judgement of study physician)
  2. Other serious adverse events (definition below)
- ACPR will be determined according to the standard WHO protocol (WHO 2003)
- Clinical and parasitological failure rates on day 3, 7, 14 and 28 will be determined according to the standard WHO protocol (WHO 2003)
- Time between inclusion and disappearance of fever
- Time between inclusion and clearance of parasites
- Change in the haematocrit after 2, 3, 7, 14 days and 28 days compared to baseline

Methods of data collection

The following laboratory methods will be employed:

Haematocrit will be measured with a centrifuge. Parasites will be diagnosed with standard techniques by light microscopy. Differentiation of recrudescences from new infections will be achieved by comparing PCR-generated *msp1* and *msp2* genotype patterns in matched pairs of isolates obtained on admission and precisely on the day of reappearance of parasitaemia.

Adverse event (AE) definition

The term “adverse event” covers any sign, symptom, syndrome, illness that appears or worsens in a subject during the period of observation in the clinical trial and that may impair the well-being of the subject. The term also covers laboratory findings or results of other diagnostic procedures that are considered to be clinically relevant.

No causal relationship with the study medication is implied by the use of the term “adverse event”. Adverse events fall into the categories non-serious and serious.

Serious adverse event (SAE) definition (GCP)

A serious adverse event is defined as any untoward medical occurrence at any dose:

(1) results in death (2) is life-threatening (3) requires inpatient hospitalisation or prolongation of existing hospitalisation (4) results in persistent or significant disability/incapacity (5) is a congenital anomaly / birth defect
(“Life-threatening” refers to an event in which the patient was at risk of death at the time of the event; it does not refer to an event which hypothetically might have caused death if it was more severe.)

Classification of severity

Mild: The adverse event does not interfere with the routine activities. The patient may experience slight discomfort.

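### Fever clearance is fixed at the first single reading below 37.5°C, with no confirmation and no rule for readings under paracetamol, so a child whose fever returns the next day still counts as cleared

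*Protocol*

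**What the plan says.** Fever clearance time is a secondary endpoint (protocol, Definition of outcomes), justified there as a standard measure that will help to plan phase III. Three places bear on how it is measured.

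- **Definitions** gives the operational rule: "Time between fever at inclusion and first temperature < 37.5°C". The same section sets D0 and D1 as calendar days and adds: "This definition is used for the endpoints ETF, LCF, LPF, ACPR and fever or parasite clearance time".
- **Assessment of secondary endpoints** lists the parameter more briefly: "Time between inclusion and disappearance of fever".
- **Treatment of subjects and clinical study procedures**, Concomitant treatments, sets the antipyretic rule: "All children having fever ≥ 38.5°C will receive standard doses of paracetamol (= acetaminophen; 10 mg/kg) until symptoms subside".

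The entry threshold is lower than the paracetamol threshold: "Axillary temperature ≥ 37.5°C" (Selection and withdrawal of subjects). The visit schedule has one examination on D0, listed before the first treatment, then morning examinations on D1, D2 and D3 in all arms, and further ones on D7, D14 and D28.

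**The concern.** One low reading ends the interval. The child need not stay afebrile, and it does not matter whether an antipyretic was given before the reading. Since the protocol itself gives paracetamol to the children with higher fever, some first low readings may reflect paracetamol and not control of the infection.

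At stake is what the endpoint means. A regimen after which fever often comes back would look the same as one that clears it for good, provided both give an early low reading. That is a poor basis for the phase III planning that the endpoint is meant to serve.

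**Working it through.** The protocol states no expected fever clearance time, so there is no figure to reproduce. The check sets the definition against the visit schedule and the paracetamol rule.

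**Step 1: which readings can end the interval.** On the documented schedule, the first examination after treatment is the morning of D1, followed by D2 and D3. In calendar days the recorded value is therefore normally D1, D2, D3 or later.

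**Step 2: every course over D1 to D3.** Write A for below 37.5°C and F for 37.5°C or more. Three examinations give 2 × 2 × 2 = 8 courses. The second column applies the protocol's rule. The third requires every later examination up to D3 to be below 37.5°C as well.

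| D1, D2, D3 | First reading (protocol) | Sustained to D3 |
| --- | --- | --- |
| A A A | D1 | D1 |
| A A F | D1 | not cleared by D3 |
| A F A | D1 | D3, unconfirmed |
| A F F | D1 | not cleared by D3 |
| F A A | D2 | D2 |
| F A F | D2 | not cleared by D3 |
| F F A | D3 | D3, unconfirmed |
| F F F | not cleared by D3 | not cleared by D3 |

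The two rules differ in 4 of the 8 courses (AAF, AFA, AFF, FAF). In all four the protocol's rule gives the earlier day. It also assigns D1 to four different courses, three of which include a return of fever by D3. The 8 courses are not equally likely, so 4 of 8 is a count of patterns and not a proportion of children.

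**Step 3: where paracetamol enters.** The rule applies at 38.5°C or more, while entry is from 37.5°C. Children who enter below 38.5°C fall outside it unless their fever rises. For a D1 reading to be lowered by paracetamol, the effect must last to that morning or dosing must have continued. The rule allows continued dosing, and no passage relates the time of a temperature reading to a dose.

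**Step 4: whether arms are treated differently.** The paracetamol rule and the morning examinations are the same in all three arms. Nothing in the text makes the shortening differ by arm.

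**Step 5: size.** This would need the share of children at 38.5°C or more, the use of paracetamol before each reading, and the frequency of courses AAF, AFA, AFF and FAF. The documents give none of these.

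**The case against.** The strongest case against the point is that it is small. The paracetamol rule is identical in three randomised arms and covers only part of the children. Concomitant drugs are already recorded (Assessment of primary endpoint). The endpoint is one of several secondary ones in a pilot trial with a safety primary, and the tests in the Statistics section are built around adverse event rates. Handling of readings under paracetamol could also be set out in an analysis plan that is not shown. All of this stands as a limit on weight. It does not remove the point, because the protocol itself fixes the single-reading definition.

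A reader might infer more than the text supports, in four ways.

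- *That a child can be recorded as cleared on D0 after a dose of paracetamol.* This needs a second D0 temperature, and none is scheduled.
- *That the methylene blue arms gain extra chances of a low reading at the evening dose.* The evening entries, such as "Treatment 2 (evening) – MB", list drug administration only. Intake is monitored by a nurse or field worker, and no temperature is mentioned. The definition does not exclude such a reading, but nothing shows that one is taken.
- *That the distortion can be stated in hours.* The Definitions section applies calendar days to this endpoint.
- *That the two wordings of the endpoint conflict.* The one under Assessment of secondary endpoints reads as a short label; the Definitions entry is the operational rule.

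Unequal paracetamol use between arms is conceivable, since blinding is stated only for laboratory technicians, but the documents do not show it.

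**Conclusion.** The point holds as a weakness in how a secondary endpoint is defined. Followed as written, the protocol counts a child as cleared on the first morning below 37.5°C even if fever is back the next morning, and it is silent on paracetamol. Relative to a sustained definition, the recorded time can only be equal or shorter, and different fever courses receive the same value, which tends to weaken contrasts between arms.

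This rests on temperatures being read at the scheduled examinations and on some children having a temporary low reading. The size cannot be derived from the documents. No bias between arms is shown, and the primary safety comparison and the sample size are unaffected. It is a cheap improvement worth making.

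**What to change.** Replace the definition as follows.

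- **Day of fever clearance:** the first scheduled morning examination among D1, D2 and D3, which all arms share, with axillary temperature below 37.5°C and with every later examination up to D3 also below 37.5°C.
- **Clearance first met on D3:** count it as D3 and flag it as unconfirmed. Do not use D7 to cancel it. With the stated tolerance of –1 and +3 days, the D7 visit can fall from D6 to D10, and an unrelated fever by then could overturn a true clearance.
- **Febrile on D3:** report as not cleared by D3.
- **By arm:** report the proportion afebrile on D1, D2 and D3, with paracetamol use before each reading taken from the concomitant drug records.
- **Sensitivity analysis:** keep the first-reading definition.

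The cost is a changed definition and a short table. No visit is added and the paracetamol rule stays as it is. The paracetamol records must be dated closely enough to place a dose before or after a reading. The downsides are that clearance first seen on D3 stays unconfirmed and that some children are dated later than now. Resolution in days is no new loss, because the protocol already applies calendar days here.

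### Haemolysis is defined by a 24-hour haemoglobin fall that the scheduled haematocrit samples cannot ascertain systematically, and its severe form has two different definitions

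*Protocol*

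**What the plan says.** The Definitions section of the protocol sets haemolysis as "Any drop in haemoglobin (Hb) of >2.5 g/dl within 24 hours".

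The visit schedule, under Treatment of subjects and clinical study procedures, lists these blood samples:

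- D0: "Capillary blood sample for a thin and thick blood film (malaria) and haematocrit", plus filter papers for G6PD genotype and parasite PCR.
- D1: an examination and treatments 3 and 4; no blood sample is listed.
- D2 and D3: parasitaemia and haematocrit.
- D7, D14 and D28: parasitaemia and haematocrit.

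The laboratory methods state that "Haematocrit will be measured with a centrifuge". They give no haemoglobin method and no conversion between the two measures. Definition of outcomes lists as a secondary endpoint "Change in haematocrit after 2, 3, 7, 14 and 28 days compared to baseline", whereas the Protocol summary names haemoglobin and haematocrit together.

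For the severe form, Definitions uses a haemoglobin limit at 5 g/dl or transfusion. Assessment of secondary endpoints, which specifies the serious adverse event (SAE) endpoint, joins the 5 g/dl haemoglobin limit by an *and* to a haematocrit limit: "15%, or received blood transfusion according to clinical judgement of study physician". The comparison signs are missing from the text as read. I treat that as a loss in extraction and rely only on the connecting words.

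Phenotypic G6PD testing and further investigations "will take place at any day between D0 and D28 in case of haemolysis".

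**The concern.** The definition needs two haemoglobin values no more than 24 hours apart. The schedule yields no haemoglobin at all, and only one pair of haematocrits at about that spacing. The longest early gap, D0 to D2, is where most of the methylene blue is given.

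The protocol itself treats haemolysis as a specific concern with this drug. The Introduction reports haemolytic anaemia in children after high intravenous doses. The concomitant-treatment rules bar other drugs that may cause haemolysis in G6PD deficiency. The exclusion criteria do not exclude G6PD-deficient children. Safety is the primary objective. If a safety event named in the protocol can be recognised only in children who happen to have an extra test, its count depends on who was tested as well as on who haemolysed. The phenotypic G6PD work-up is triggered by the same event.

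The two severe definitions raise a separate problem: the same child could be counted under one and not the other, and the stricter version feeds a listed secondary endpoint.

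**Working it through.** The plan gives no figure on this point to reproduce. The check compares the sampling times with the 24-hour window, then asks what a measured fall can establish.

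**Inputs.** Sampling days and the morning visits come from the visit schedule. Treatment 1 is given before 14:00 on D0. D7, D14 and D28 carry a tolerance of −1 to +3 days (Definitions). Two clock times are my assumptions: morning means 08:00, and the D0 sample is taken between 08:00 and 14:00.

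**Gaps between consecutive scheduled samples.**

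| Pair | Gap |
| --- | --- |
| D0–D2 | 48 h (D0 at 08:00) to 42 h (D0 at 14:00) |
| D2–D3 | 24 h |
| D3–D7 | 96 h nominal; at least (6 − 3) × 24 = 72 h |
| D7–D14 | 168 h nominal; at least (13 − 10) × 24 = 72 h |
| D14–D28 | 336 h nominal |

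Only D2–D3 fits the window. D0 to D3 lasts 66–72 h, so the share covered is 24/72 = 33% to 24/66 = 36%.

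**Doses.** Methylene blue is given twice daily for three days, which is 6 doses. Treatments 1 to 4 precede the D2 sample, which is listed before treatment 5. So 4 of 6 doses fall in the gap that has no scheduled 24-hour pair.

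**Conversion.** Read literally, no scheduled pair can satisfy the definition, because none measures haemoglobin. Suppose haematocrit is converted. Pairing 5 g/dl with 15% implies 15/5 = 3 points per g/dl, so 2.5 g/dl is 2.5 × 3 = 7.5 points. If 2.8 to 3.2 points per g/dl is assumed (a range not in the protocol), the result is 7.0 to 8.0 points.

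**What a D0–D2 fall can show.** Split an interval of at most 48 h into two parts of at most 24 h each.

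- Net fall above 5 g/dl (5 × 3 = 15 points): at least one part must contain more than 2.5 g/dl, so the criterion was met.
- Net fall between 2.5 and 5 g/dl (7.5 to 15 points): undetermined. A fall of 4 g/dl may be 2 + 2, which does not meet the rule, or 4 + 0, which does.

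As an illustration, a fall from 36% to 24% between D0 and D2 is 12 points, or 12/3 = 4 g/dl. With 2.8 to 3.2 points per g/dl it is 12/2.8 = 4.3 to 12/3.2 = 3.75 g/dl. On each of these ratios it lies in the undetermined band.

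**Severe form, side by side.**

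| Section | Rule |
| --- | --- |
| Definitions | haemoglobin limit, or transfusion |
| Assessment of secondary endpoints | haemoglobin limit and haematocrit limit, or transfusion |

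Scheduled data contain no haemoglobin, so as written neither non-transfusion limb can be evaluated from them. A haematocrit at the 15% limit does not by itself complete the second rule unless a conversion is stated.

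**The case against.** The strongest reply is that little is lost apart from a label. The 24-hour definition is not a listed primary or secondary endpoint. The primary endpoint is adverse events, and the haemolysis item within the SAE endpoint uses a level or a transfusion. A large D0–D2 fall would be reported in the haematocrit-change endpoint. It can also count as an adverse event, since that definition covers clinically relevant laboratory findings and surveillance includes laboratory results. A physician examines every child on D1, and extra tests can be had round the clock. G6PD genotype is collected on D0 whether or not haemolysis occurs. If 5 g/dl and 15% are equivalent, the *and* in the severe rule adds nothing, and transfused or hospitalised children qualify by other routes.

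Most of this stands, and it limits the point. A reader might infer that the trial cannot see haemolysis, that it would report almost none, or that no D0–D2 fall could ever satisfy the rule. The documents support none of these readings: the haematocrit-change endpoint, the unscheduled tests and the 5 g/dl argument in the working each contradict them.

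The objection does not make the definition usable. Tests prompted by symptoms are not systematic, and the protocol describes blinding only for laboratory technicians, so the decision to test could differ by arm. Equivalence of the two severe limits is an inference, because the protocol states no conversion.

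**Conclusion.** The point holds in a limited form. Haemolysis as defined cannot be ascertained systematically from the scheduled samples: no haemoglobin is scheduled, D1 has no sample, and one pair covers 33–36% of D0 to D3. After conversion, D0–D2 falls of about 7.5 to 15 haematocrit points remain unclassifiable, although they are visible in the haematocrit-change endpoint. The severe form is inconsistent between Definitions and the SAE endpoint, and both versions call for a measurement that is not scheduled.

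The gap lengths rest on the assumed clock times, and the point values on the 3:1 ratio implied by the protocol; the range of 2.8 to 3.2 moves 2.5 g/dl only between 7 and 8 points. The sample size and the primary comparison do not depend on this definition. I would therefore rate it as something that should be fixed, preferably before enrolment because values not measured cannot be recovered later, rather than as a defect that invalidates the design.

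**What to change.** Reconcile the Protocol summary, Definitions, Definition of outcomes, the visit schedule and Assessment of secondary endpoints on three matters.

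- **One analyte.** If haematocrit is what will be measured, say so throughout, and state the haemoglobin-to-haematocrit conversion wherever a limit is given in g/dl.
- **One analysis definition of haemolysis.** Base it on the haematocrit fall from D0 to D2 or from D0 to D3, with the limit expressed as the converted equivalent of the protocol's own 2.5 g/dl. Leave out the D7 to D28 intervals, where slow anaemia would be mixed with acute haemolysis.
- **One severe definition.** Use the same wording in both sections, in a form that the scheduled data can satisfy.

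The sponsor should also reconcile the clinical trigger for phenotypic G6PD testing with the schedule. That is a clinical decision, and I propose no threshold for it.

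The cost is protocol wording and analysis specification, using samples already planned. The drawback is that a 2- to 3-day interval also captures some malaria-related falls. These arise after randomisation and may differ by arm through parasite clearance, so randomisation does not simply balance them, and the comparison should be read alongside the parasitological outcome. Keeping the 24-hour window instead would require a D1 sample, and still a haemoglobin measurement or a stated conversion.
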